## Abstract

**Background:**

Childhood stroke is a rare but potentially life-threatening event that can occur at any age. It requires prompt diagnosis and appropriate treatment, and, in view of the frequent neurological and neurocognitive sequelae, long-term care in a multidisciplinary and multiprofessional setting. The management of stroke in children, which differs in many aspects from stroke in adults, often relies on local expert opinions and retrospectively collected data rather than high-quality evidence from prospective randomized controlled clinical trials, especially in the acute phase.

**Aims:**

The **Pediatric Registry for Stroke as a Multidisciplinary Approach to healthcare research (PRiSMA)** study aims to systematically collect longitudinal prospective observational data across the acute and long-term phases to optimise diagnosis, personalised acute therapy, neurorehabilitation, and prevention of recurrent stroke. The data will inform development of further hypothesis-driven studies of childhood stroke in national and international networks.

Furthermore, PRiSMA will facilitate case-specific collaboration within the registry network, allowing treating clinicians to consult experienced colleagues on complex cases.

**Methods:**

In PRiSMA all children and adolescents (>28 days of life, ≤ 18years) with arterial ischemic stroke (AIS) or hemorrhagic stroke (HS) are eligible for recruitment. The nationwide multicenter, systematic data collection is performed in the acute and chronic phases, extracted from patient medical records supplemented by direct registry-specific medical history provided by caregivers. In addition, a questionnaire-based data on quality of life and behaviour will be collected. International collaborations are established across Germany, Austria and the Netherlands.

**Status:**

Currently, 16 centres in Germany and 1 centre in Austria have commenced recruitment. 30 patients are currently (17 Nov 25) enrolled after arterial ischaemic stroke and 1 after haemorrhagic stroke.

## Introduction

Paediatric stroke can occur at any age and is one of the most time-critical emergencies in paediatric and adolescent medicine. Many of those affected have long-term neurological impairments, such as hemiparesis and epilepsy [1,2]. However, the neurocognitive effects on behaviour and well-being should not be underestimated, as they have a significant impact on a child’s ability to engage in normal activities [3–5].

Evidence-based diagnostic algorithms and treatment recommendations are available for adult stroke where new models of care, such as neurovascular networks, have been successful, and stroke units have been established throughout Germany. However, these extensive, dynamic and positive experiences in adult neurology cannot simply be transferred to the paediatric population due to the specificities of a child’s developing brain and the fundamentally different aetiologies of stroke in children [6–8].

The approach to paediatric stroke, as a rare disease, is often empirical and based on the expert opinions and retrospectively collected observational data. Furthermore, prospective clinical trials, particularly in the acute phase of paediatric stroke, are often not thought feasible [9,10].

In Germany there is a paucity of comprehensive scientific analysis with systematic assessment of patient data in the acute and long-term phases, which could form the basis for optimised diagnostics, personalised acute therapy, recurrence prevention and neurorehabilitation. This underscores the need for systematic, prospective data collection to improve diagnostics and outcomes. We therefore need reliable data that also includes follow-up information on these patients and their treatment.

## Materials and methods

### Aims

The primary aim of the multicentre PRiSMA study is to prospectively collect longitudinal data that will enable a broad range of research questions to be addressed in the fields of epidemiology, healthcare provision, therapy, and prognosis. These questions include, but are not limited to, identifying prognostic and risk factors for paediatric stroke; evaluating quality of life over the course of the disease; comparing the application of different acute and secondary preventive therapies nationally and across Europe; and describing the quality and speed of initial diagnosis and acute care. The findings from the collected data will translate to improvements in acute and long-term care, leading to the adaptation and further development of childhood stroke guidelines.

The collected data will also support subsequent hypothesis-driven studies aimed at identifying children at particularly high riskof stroke and ensure they receive earlier, personalised intervention. Another important aim of PRiSMA is to build a consultation network. Modern medicine increasingly relies on interdisciplinary networking. In everyday clinical practice, many paediatricians only see and treat a few children with strokes, who may differ from each other in terms of clinical presentation, aetiology, course and treatment requirements. PRiSMA will facilitate professional exchange between paediatric neurologists, thus contributing directly to improving medical care for children with this rare disease.

Lastly, planned awareness campaigns targeting caregivers and emergency department physicians are intended to improve care for children by enabling earlier stroke diagnosis.

### Procedure

The PRiSMA paediatric stroke registry is a multicentric, observational cohort study. So far 17 hospitals treating paediatric stroke patients are participating and enrolling patients. Further 6 centres are in the process of contract and ethics approval. In the first step, the study covers Germany as well as Austria and the Netherlands. Further European and international collaborations are planned.

Patients are recruited to the registry by the treating clinician at each study centre who obtains signed informed consent. Clear, age-appropriate informational materials are provided to the patient and their parents or legal representatives. Enrolment in the registry occurs only after obtaining a written informed consent form from the patient and their legal guardians. In accordance with data protection laws, a patient can withdraw his or her consent at any time.

If the patient and parents agree, they may be contacted by the coordinating study centre in Munich for a questionnaire-based survey on quality of life (QoL) and behaviour. A separate written informed consent is required for this component of PRiSMA.

### Study population

Internationally, the incidence of stroke in children is reported to be 1–8 per 100,000 children [11,12], but reliable data for Germany are lacking. Based on data from the German Federal Statistical Office, around 14 million people under 18 years live in Germany [13], which would expect 140–1120 cases of paediatric stroke per year. Considering the findings from the nationwide, multicentred ESPED study [1] into account, we would include approximately 55 patients with ischemic stroke annually, along with those newly diagnosed with haemorrhagic stroke. Including the patients from Austria and the Netherlands, approximately 100 patients per year can be expected to be enrolled. As an extension to other European countries is intended, the number should further increase in the future.

### Inclusion and exclusion criteria

Prospectively included are all children and adolescents (>28 days to 18 years of age) with radiologically confirmed arterial ischemic (AIS) or haemorrhagic stroke (HS) (first event or recurrence).

Exclusion criteria are acute symptomatic neonatal stroke, suspected perinatal stroke diagnosed beyond the neonatal period, traumatic brain haemorrhage, and infarction (haemorrhagic or ischemic) secondary to sinus or cerebral vein thrombosis. In the absence of consent, inclusion is not possible.

### Data collection

1
**Medical data**

The data collected are observational, relying primarily on medical records as the source of information. Data are collected prospectively, with the exception of information with regard to stroke risk factors prior to the index event, which have to be collected retrospectively.

For each patient, we are interested in timelines of care for the index or recurrent stroke event. Additionally, follow-up information is collected at three to six months and twelve months after stroke, and then annually until the patient reaches adulthood. These intervals correspond to the usual clinical follow-up appointments (see Fig 1).

**Fig 1 pone.0341646.g001:**
[figure not shown]
Time points of data collection. **CBCL** – Child Behavior Checklist, **KINDL** – quality of life questionnaire, **QoL** – Quality of Life.

Data collection will be aligned with routine clinical appointments, to minimize research burden on families. If there is no doctor-patient contact on any of the proposed dates, no entry can be made in the registry. Data is entered into the database directly by the centres. An overview of collected data for both AIS or HS is shown in the Table 1.

**Table 1 pone.0341646.t001:** Overview of collected data of children with arterial ischemic stroke (AIS) or haemorrhagic stroke (HS) (categories, further details available on request).

CRF		
	**Data category**	**Details on**
**Acute**	Demographics	Age, sex, ethnicity, residence degree of urbanisation
	History of stroke event	Time of onset Clinical symptoms
	Medical history and previous development	Pre-existing conditions Development normal/with concerns
	Family history	Risk factors for stroke, cardiovascular/ thrombotic/ bleeding events in family members < 50 years of age
	Clinical examination at admission	GCS AWUP PedNIHSS Vital parameters (HR BP, temperature, ….)
	Neuroimaging (AIS)	Time of neuroimaging Modality (cCT, cMRI, cMRA,…) Results (incl. localization, affected vessel, results of vesselwall imaging, DWI/FLAIR mismatch, etc)
	Neuroimaging (HS)	Time of neuroimaging Modality (cCT, cMRI, cMRA,…) Bleeding volume (IVH: Graeb Score, SAH: Fisher Scale) Further specification: Aneurysm, AVM (Spetzler-Martin scale), cavernoma, dissection, angiopathy,…
	Diagnostic work up	Neurophysiology (i.e., EEG…) Cardiac work up (ECG, TTE, TEE) Laboratory testing (BC, vasculitis, coagulation, infectious, genetic testing)
	Acute Treatment (AIS)	Time of intervention Recanalization (thrombolysis, thrombectomy), antithrombotic treatment, immunosuppression etc.
	Acute Treatment (HS)	Time of intervention Interventional neuroradiology Neurosurgery
	Clinical course	Complications (arterial hypertension, seizures, increased intracranial pressure, infection)
	time of discharge clinical symptoms Treatment Follow up	Neurological examination, mRS Antithrombotic treatment, immunosuppression, ASM, other rehabilitation
	Stroke classification (AIS)	CASCADE criteria
	Stroke classification (HS)	ICH, IVH, SAH i.e., AVM, cavernoma, aneurysm, tumor, hypertension, medication induced, coagulation disorder, other
**Follow-up**	Demographics	Age at follow up
	Full recovery after stroke? (subjective)	Yes/no (further specification)
	childcare, school	Special educational needs?
	Aspects of social law	Level of care, Severely disabled pass
	Transition (for adolescent patients)	
	Family history	Any new aspects not reported above?
	Intermittent diagnostics	Neuroimaging, laboratory/genetic testing, cardiac test, neurophysiology, neuropsychology,…
	Medication	Antithrombotic treatment Immunosuppressive treatment Antiseizure medication other
	Functional therapies	i.e., speech therapy, physiotherapy, OT, psychotherapy
	Intermittent interventions/surgery	i.e., interventional neuroradiology, neurosurgery, cardiac surgery
	Neurological examination	Neurological sequelae mRS GMFCS, MACS, BFMF, CFCS,…
	Stroke classification	Any change in diagnosis?
**Recurrent stroke**	Demographics	Age at stroke recurrence
	History of stroke	Time of Onset Clinical symptoms
	Clinical examination at admission	GCS AVUP PedNIHSS Vital parameters (HR, BP)
	Neuroimaging (AIS)	Time of neuroimaging Modality (ccT, cMRI, cMRA,…) Results (incl. localization, affected vessel, results of vesselwall imaging, DWI/FLAIR mismatch, etc)
	Neuroimaging (HS)	Time of neuroimaging Modality (ccT, cMRI, cMRA,…) Bleeding volume (IVH: Graeb Score, SAH: Fisher Scale) Further specification: Aneurysm, AVM (Spetzler-Martin scale), cavernoma, dissection, angiopathy,…
	Current medication	Antithrombitic treatment Immunosuppressive treatment Antiseizure medication other
	Acute Treatment (AIS)	Time of intervention Recanalization (thrombolysis, thrombectomy), antithrombotic treatment, immunosuppression etc
	Acute Treatment (HS)	Time of intervention Interventional neuroradiology neurosurgery
	Clinical course	Complications (arterial hypertension, seizures, increased intracranial pressure, infection,…)
	time of discharge - clinical symptoms - Treatment	Neurological examination, mRS Antithrombotic treatment, immunosuppression, ASM, other

**ASM** – Antiseizure Medication, **AVM** – Ateriovenous Malformation, **AVUP**- Alert Verbal Unresponsive Pain, **BFMF** – Bimanual Fine Motor Function, **BP** – Blood Pressure, **CASCADE** – Childhood AIS Standardized Classification and Diagnostic Evaluation, CFCS – Communication Function Classification System, **GCS** – Glasgow Coma Scale, **GMFCS** – Gross Motor Function Classification System, **HR** – Heart Rate, **ICH** – Intracranial Haemorrhage, **IVH** – Interventricular Haemorrhage, **MACS** – Manual Ability Classification System, **mRS** – modified Rankin Scale, **OT** – Occupational therapy, **PedNIHSS** – Pediatric NIH Stroke Scale, **SAH** – Subarachnoidal Haemorrhage

2

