### Statistical analysis

The PRiSMA registry serves both to answer important questions and to generate new hypotheses exploratively.

Main outcome measurements are mortality, risk of recurrence, quality of life (measured via the KINDLR), behavioural and emotional function (measured via the CBCL) and neurological deficit and function (mRS, GMFCS, MACS, etc).

Continuous variables are described using the median and interquartile range or the mean and standard deviation. Categorical variables are described using relative and absolute frequencies. Event time data are described using Kaplan-Meier curves. In the presence of competing events, such as the occurrence of a recurrence and mortality without a prior recurrence, cumulative incidence curves considering both risks are used.

To identify prognostic factors, appropriate multiple regression models are conducted like linear, logistic, Cox proportional hazards or Fine and Gray model. If necessary, multiple imputation procedures for missing values have to be used.

Analyses will be performed with either SAS or R.

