## Outlook

To minimise loss to follow-up, we are developing a minimal data set questionnaire, which will be sent to families alongside the QoL questionnaires. This will enable us to obtain basic information regarding therapy and diagnostics even if children and adolescents no longer have regular medical appointments or have moved to predominantly outpatient care, for which no entries are made in the register after some time.

Further satellite studies are planned, including investigations into the genetic predisposition to childhood stroke.

We also plan to capture data about spinal stroke via PRiSMA which are even rarer than cerebral infarcts in childhood and adolescence. They can cause permanent damage to the spinal cord and lead to long-term disabilities [24–26]. Currently, there are limited published data on spinal infarcts in this age group, and no systematic long-term surveys have been conducted.

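### A death outside a registry-centre contact has no described route into the registry, although mortality is a main outcome

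*Protocol article*

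**What the plan says.** The Medical data section schedules follow-up at three to six months, at twelve months, and "then annually until the patient reaches adulthood". The text under Fig 1 ties entries to these visits: "If there is no doctor-patient contact on any of the proposed dates, no entry can be made in the registry". It also says who makes them: "Data is entered into the database directly by the centres".

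The Statistical analysis section states: "Main outcome measurements are mortality, risk of recurrence, quality of life", followed by behavioural and functional measures. It plans Kaplan-Meier curves for event times. For competing events, "such as the occurrence of a recurrence and mortality without a prior recurrence, cumulative incidence curves considering both risks are used".

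The Outlook section acknowledges that some children leave regular care or move to mainly outpatient care, "for which no entries are made in the register after some time". It announces a minimal data set questionnaire to limit this loss. The Limitations section discusses missing values, unknown coverage and the lack of central imaging review. It does not mention deaths that go undetected.

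**The concern.** For most follow-up items, a missed visit means a missing value. For mortality, the event itself prevents the visit. A child who dies between two scheduled dates cannot attend the next one, and the rule then allows no follow-up entry. The record ends in the same way as that of a child who is well and has stopped attending.

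The planned curves need dated deaths. If some deaths are unknown, those children are censored although they have had the event. Censoring then depends on the outcome, and the mortality curve lies too low. The same deaths are missing as the competing event in the recurrence analysis. Follow-up can run for many years, so the share of mortality exposed to this gap grows with time since discharge.

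**Working it through.** **Is there another way in?** These are the routes the article describes, checked against a death at home or in a non-participating hospital.

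- *Recurrent-stroke form (Table 1).* It is tied to an event and includes clinical course and mRS at discharge. A death during a recurrence admission at a participating centre can be entered. Other deaths are not covered.
- *Mailed KINDL and CBCL questionnaires (Data on Quality of Life and behavior).* Families are still contacted when they no longer attend. The survey needs a separate consent (Procedure) and is described for quality of life and behaviour. A reply may reveal a death, but no survival item is described.
- *Minimal data set questionnaire (Outlook).* It is still being developed. Its stated content is therapy and diagnostics.
- *Pseudonym linkage (Data management).* It joins records between institutions that enter data. No link to a death register is described.
- *Multiple imputation (Statistical analysis, Limitations).* It fills missing values in known records. It does not restore a death that nobody knows occurred.

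None of these is said to collect survival status.

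**Direction.** The article sets no censoring date. If silent patients are censored at last contact, their unrecorded deaths drop out of the event count. If they are instead counted as alive up to the analysis date, those deaths are still not counted and the risk set is larger. Mortality is biased downward either way.

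**Size.** The article gives no mortality, recurrence or loss rate, so there is no figure of its own to reproduce on this point. The following is an illustration, and all rates are assumptions:

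- h = in-hospital mortality, 3% or 5%
- d = 5-year mortality after discharge, 1% to 10%, with constant hazard
- a = share of post-discharge deaths that are recorded; the rest are censored at last contact

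True 5-year mortality = 1 − (1 − h)(1 − d). Observed = 1 − (1 − h)(1 − d)^a. Deaths missed per 100 enrolled at a = 0 are 100(1 − h)d.

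| h | d | True | Observed, a = 0 | Observed, a = 0.5 | Missed per 100, a = 0 |
|---|---|---|---|---|---|
| 3% | 1% | 3.97% | 3.00% | 3.49% | 0.97 |
| 3% | 5% | 7.85% | 3.00% | 5.46% | 4.85 |
| 3% | 10% | 12.70% | 3.00% | 7.98% | 9.70 |
| 5% | 1% | 5.95% | 5.00% | 5.48% | 0.95 |
| 5% | 5% | 9.75% | 5.00% | 7.41% | 4.75 |
| 5% | 10% | 14.50% | 5.00% | 9.88% | 9.50 |

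Example for the first row: 1 − 0.97 × 0.99 = 0.0397. With a = 1 the true value is recovered. The Study population section expects about 100 enrolments a year, so the last column is also the number of deaths missed per yearly cohort over five years.

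**Recurrence.** Let r be the assumed 5-year net recurrence, λr = −ln(1 − r)/5 and λd = −ln(1 − d)/5. The true cumulative incidence is λr/(λr + λd) × [1 − (1 − r)(1 − d)]. If all competing deaths are unrecorded and censored, the estimate is r.

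- r = 10%, d = 1%: 9.95% against 10.0%, a difference of 0.05 points.
- r = 20%, d = 10%: 19.02% against 20.0%, a difference of about 1 point.

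This covers only the missing competing deaths. Recurrences that are never reported would act in the other direction, and the documents give no basis for a figure.

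**The case against.** The strongest reply is that the article is a summary and the rule is being read too literally. It concerns the scheduled follow-up dates, not every possible entry. The recurrent-stroke form is triggered by an event, medical records are the main source, missing values are queried, and the authors name loss to follow-up and are building a questionnaire against it. The registry is also partly exploratory.

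Much of this stands, and it rules out several stronger readings:

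- *The case report form has no death field.* A reader might infer this from Table 1, whose follow-up items presuppose a living child. The table describes itself as an overview of categories with details available on request, so the absence of an item there proves nothing.
- *All deaths after discharge are lost.* Some can enter through a recurrence admission at a participating centre, and some may become known through the mailings.
- *Recurrence is affected as badly as mortality.* Recurrence has its own form. An event treated elsewhere can surface at the next visit, or by linkage if that hospital participates. It is missed mainly when the child never returns.
- *The plan censors at the last scheduled visit.* It names no censoring date, and that detail commonly belongs in the analysis plan.
- *Mortality ranks above the other outcomes because it is listed first.* The article states no ranking.

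The reply does not remove the point itself. The restriction on entries is stated, not merely left out. Even if the full form contains a death field, the rule as worded would not allow a follow-up entry to be made without a contact. Querying missing values does not help if the answer may not be entered.

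**Conclusion.** The point holds in limited form. The entry rule and the mortality outcome do not fit together. A death after discharge and outside a registry-centre contact has no described route into the registry and looks like loss to follow-up. Censoring is then informative and mortality is biased downward. The direction follows from the documents, but the size does not.

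Under the assumed ranges, true 5-year mortality of 4.0 to 14.5% would appear as 3 to 5% if no post-discharge death were recorded, and as 3.5 to 9.9% if half were. Any single multiple quoted for the underestimate would rest wholly on such assumptions, and one computed on post-discharge deaths alone would overstate the effect on total mortality. The distortion of recurrence incidence from missing competing deaths is at most about 1 percentage point in the same ranges.

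This is a cheap and worthwhile improvement to ascertainment. It does not show that the registry's other outcomes are unsound.

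**What to change.** 1. Change the entry rule under Fig 1. At each scheduled time point the centre completes a short status line even without a visit: alive, dead or unknown; date last known alive; date of death and source of the information; recurrence since the last entry; reason for no visit.
2. Allow a death to be entered at any time, independent of the visit schedule.
3. Add survival and recurrence items to the minimal data set questionnaire, and make sure the consent covers it. It is to be sent with the quality-of-life questionnaires, which need a separate consent, so otherwise it may reach only part of the cohort.
4. State the censoring rule: date last known alive for mortality, and date last known alive and recurrence-free for recurrence.
5. Name under-ascertainment of deaths in the Limitations section.

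If the full case report form already allows a death entry without a visit, correcting the sentence under Fig 1 and describing that route would cover items 1 and 2 in part.

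The cost is one short REDCap form, a few sentences of protocol text, and a few minutes of chart check or a phone call per missed visit. A change to the protocol or consent that counts as significant would go to the review board, as the article already provides. With 31 patients enrolled by 17 Nov 25, little has to be filled in retrospectively. Dates of death and dates last known alive become harder to recover later.
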